### **Recruitment & Screening**

#### **Recruitment**

Prior to initiation of study recruitment procedures, healthcare providers at each site will be notified about the study and informed that patients enrolled in the study may be bringing summary sheets generated by the decision aid to clinic visits to facilitate discussions about their postpartum contraceptive decisions or decision-making process. Similar language and procedures will be used to communicate with providers across all sites in advance of the study, including emails and brief presentations during staff meeting times. Of note, the decision aid will not be shown or explained in substantial detail to avoid influencing the standard of care.

Using a combination of in-person and remote methods initiated due to COVID-19), we will **recruit 350 pregnant women** with Medicaid coverage who are contemplating a postpartum sterilization. To **optimize the racial/ethnic and geographic diversity** of our sample, the study will recruit at Magee-Women's Hospital (MWH) in Pittsburgh, Pennsylvania; University of Tennessee Medical Center (UTMC) in Knoxville, TN; Zuckerberg San Francisco General Hospital (ZSFG) in San Francisco, California. All three sites serve large numbers of low-income women. At these clinical sites, we will employ **recruitment strategies** that we have previously used to successfully recruit pregnant and reproductive-aged women, including posting study flyers throughout each clinic, asking clinical staff to refer potentially eligible women, displaying on message boards and hospital display screens, advertising on Pitt+Me (a University of Pittsburgh research registry), and Craigslist. Pre-COVID, clinic staff were stationed in each of the clinic sites to the clinic waiting rooms to facilitate enrollment during clinical visits.

The COVID-19 pandemic required recruitment redesign. To facilitate remote recruitment in the COVID era, in addition to flyers and message boards, each site will utilize electronic medical records (EMR) to identify potentially eligible persons. This process will vary by site based on local IRB and institutional guidelines for research recruitment of patients and are detailed below:

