Since study staff at UPMC are still recruiting in-person (unlike MWH and ZSFG which are using entirely remote recruitment procedures), patients at UPMC will have completed COVID-19 screenings during their regularly scheduled visit and will not have to complete a separate COVID screening by study staff. If a potential participant is recruited in-person but does not have time to complete all of the screening, consent, and initial study activities (randomization, baseline assessment, intervention, and T1 assessment) at that time, research staff should conduct the pre-screening assessment and verbal consent to collect contact information and set up another appointment. If a potential participant is recruited in-person, and they express interest in the study but do not have time for any assessment including pre-screen questions, study staff may ask for verbal consent to collect contact information. During the follow-up call, study staff should complete the pre-screen assessment and, if preliminarily eligible, schedule an appointment for the rest of the initial study activities.

For participants that choose to participate remotely, a telephone and/or videoconference appointment will be scheduled and conducted at the participant's convenience. During this appointment, a full screening will be conducted to ensure the participant is still eligible. Verbal consent will be obtained to conduct the full screening questions over the phone. Informed consent, baseline assessment, the intervention, and Time 1 assessment will then be conducted remotely over the phone or videoconference.

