    - Provider sterilization counseling between T1 and T3 (composite variable of this question at T3 about counseling during this pregnancy isolating those who said they already received this counseling prior to or during this pregnancy at baseline)
    - Provider contraceptive counseling between T1 and T3
    - Medicaid consent signed between T1 and T3
    - Provider sterilization and/or Medicaid consent between T1 and T3

- **Subgroup Analyses (Interactions, no *a priori* hypothesis, not powered) of the Primary Outcomes by:**

*Regression model needs to control for site, including direct effects of the decision aid and the variable of interest below. Check for collinearity (VIF with a cut-off of 10)*

- Race/ethnicity (non-Hispanic Black, non-Hispanic White, Hispanic, non-Hispanic Other)
  - **Knowledge=decision aid + site + race/ethnciity + DA#Race/ethnicity**
  - **Decisional conflict= decision aid + site + race/ethnciity + DA#Race/ethnicity**
- Age (categorized for this analysis: <25, 25+)
  - **Knowledge= decision aid + site + age + DA#age**
- Completed Decision Aid in-person or virtual
- Recruitment Site (California, Pennsylvania, Tennessee)
- Language of the consent form (English vs Spanish)
- Education level (HS or less including GED vs. any post-high school or more)
- Provider counseling/consent form signed at T1
  - Provider sterilization counseling at baseline (before this pregnancy, during this pregnancy)

- **Participant Satisfaction with Current Contraceptive Method(s) at Time 3:** Compared to women who receive usual care alone, women randomized to the decision aid arm will report greater satisfaction with their current contraceptive method(s) at Time 3

- **Desire for sterilization:** variable will be used to assess baseline differences (pre-decision aid for intervention group, T1 for control), changes from baseline to T1 for intervention groups, and differences between post-decision aid for intervention group vs T1 for control group.

- To test exploratory hypotheses, we will first use linear regression (using the continuous measure 1-5 where higher score indicates higher desire for sterilization) to test intervention effects (pre-intervention baseline vs post-intervention T1; post-intervention vs T1 control), controlling for study site.

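### The exploratory subgroup models include site only as a main effect, so part of any site difference in the aid's effect can appear as effect modification by language, delivery mode or race/ethnicity

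*Combined protocol and SAP*

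**What the plan says.** Under Exploratory Hypotheses, the subgroup analyses of the primary outcomes carry this modelling instruction: "Regression model needs to control for site, including direct effects of the decision aid and the variable of interest below". Three formulas follow:

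- "Knowledge=decision aid + site + race/ethnciity + DA#Race/ethnicity"
- "Decisional conflict= decision aid + site + race/ethnciity + DA#Race/ethnicity"
- "Knowledge= decision aid + site + age + DA#age"

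None has a DA#site term. No formula is written for the other modifiers, so the general instruction governs them. Those modifiers include in-person or virtual completion, language of the consent form, education, and "Recruitment Site (California, Pennsylvania, Tennessee". The one diagnostic is "Check for collinearity (VIF with a cut-off of 10", with no consequence stated for exceeding it. The analyses are labelled as having no prior hypothesis and as not powered.

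Other sections bear on which modifiers follow site. Inclusion Criteria admits Spanish speakers at San Francisco only. The covariate table has delivery mode noted by staff at the Tennessee site, where both modes are in use. Recruitment says the three sites were chosen to "optimize the racial/ethnic and geographic diversity", but gives no race/ethnicity distribution by site.

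**The concern.** A site main effect removes differences between sites in the level of knowledge or decisional conflict. An interaction test asks about differences in the aid's effect, and controlling that for site requires DA#site. Without it, a modifier that is distributed unevenly across sites picks up part of whatever makes the aid work better or worse at one of them.

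What is at stake is interpretation. A difference that belongs to a site could be read as the aid working less well in one ethnic or language group. For a tool motivated by reproductive equity, that would be an unfortunate misreading. The label of not powered warns about imprecision; it does not warn about this.

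**Working it through.** **Inputs from the documents.** 1:1 allocation stratified by site (Randomization); three sites, 350 women, d = 0.46 and 0.36, two-sided alpha 0.025, 15% attrition (Sample Size Calculation); 97.5% intervals (Exploratory Hypotheses).

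**Assumed, because the documents do not give them.** Site sizes (equal, or 45/35/20), race/ethnicity mix by site, and any site difference in the aid's effect.

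**1. The plan's own figure.** For d = 0.36: n = 2(2.2414 + 0.8416)²/0.36² = 146.7, so 147 per arm; 147/0.85 = 172.9, so 173, against 175 stated. The design figure reproduces. The plan states no figure for the subgroup models.

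**2. Share transferred.** Let the aid's effect differ by δ at San Francisco (SF), with no true modification by M. With 1:1 allocation unrelated to site and M, the planned DA#M coefficient estimates

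δ × [P(SF | level of M) − P(SF | reference level)].

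The bracket is the share credited to the modifier. It is 0 when M is unrelated to site.

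**3. Language.** With equal sites and a fraction p of SF participants Spanish-speaking, P(SF | Spanish) = 1 and P(SF | English) = (1−p)/(3−p), so the share is 2/(3−p).

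| p | Share to DA#language | Largest VIF, planned model |
|---|---|---|
| 0.20 | 2/2.80 = 71% | 2.2 |
| 0.50 | 2/2.50 = 80% | 2.7 |
| 0.80 | 2/2.20 = 91% | 4.7 |
| 0.95 | 2/2.05 = 98% | 14.7 |

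**4. Race/ethnicity.** A two-level illustration with equal sites and 10% Hispanic at each of the other two sites:

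- 48% Hispanic at SF: 0.48/0.68 − 0.52/2.32 = 0.706 − 0.224 = 0.48.
- 65% Hispanic at SF: 0.65/0.85 − 0.35/2.15 = 0.765 − 0.163 = 0.60.

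With the plan's four categories and non-Hispanic White as reference, over both sets of site sizes, the share credited to DA#Hispanic is 0% (no link), 40-47% (mild assumed link), 69-75% (moderate) and 85-89% (strong). For DA#Black it is 3-9% across the three linked mixes.

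**5. False positives.** Simulated joint test of DA#race/ethnicity at 0.025, N = 350, equal sites, SD 1, 3,000 runs (Monte Carlo SE at the nominal rate √(0.025 × 0.975/3000) = 0.3 percentage points):

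| Site difference | No link | Mild | Moderate | Strong |
|---|---|---|---|---|
| 0.23 SD | 2.6% | 3.1% | 4-5% | 5% |
| 0.46 SD | 2.5% | 4.9% | 12% | 17% |

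A reduction of 0.46 SD means the whole planned knowledge effect vanishing at one site; 0.23 SD is half of it. With DA#site added, the share is 0 and the rate is 2.1-3.2% throughout.

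**6. Precision cost.** SE of DA#Hispanic in SD units, equal sites, without and with DA#site: 0.277 to 0.301 (ratio 1.09, mild), 0.266 to 0.354 (1.33, moderate), 0.257 to 0.454 (1.77, strong).

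**7. VIF.** It is computed from the included predictors alone, so it takes the same value whether or not the aid's effect differs by site. In the planned race/ethnicity models the mean of the largest VIF was 3.0-5.1, and it exceeded 10 in at most 0.1% of runs. It also depends on the reference group: the VIF of the arm term is 1/(reference share). If 8% of women were under 25 (an assumption), that is 1/0.08 = 12.5 with under-25 as base and 1/0.92 = 1.09 with 25+ as base. For DA#age the values are 0.2484/0.0184 = 13.5 and 0.0384/0.0184 = 2.1. The interaction test is the same under both codings.

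**The case against.** The strongest reply is that these analyses are exploratory and unpowered, no causal claim about any modifier is planned, and site, language and delivery mode are each examined in the same set. A marginal DA#race/ethnicity term also answers a legitimate descriptive question: whether the effect differed across groups in this sample. All of that stands, and it limits the weight of the point. But testing site separately does not adjust another interaction for it.

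Several stronger readings are tempting, and the documents do not support them.

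- *Any site difference is credited to the modifier in full.* Only a share is, and it is zero without a link.
- *Race/ethnicity is tied to site.* Choosing sites for diversity does not establish this; each site could itself be diverse.
- *The aid was delivered differently across sites.* The remark "unlike MWH and ZSFG which are using entirely remote recruitment procedures" concerns recruitment. The Screening section lets participants choose in-person or remote procedures and describes in-person participation at Pittsburgh and San Francisco.
- *Differing usual care would drive a site difference.* This route is weak. Controls complete T1 straight after randomization, and the usual-care description places most consent-form completion later, at 24-32 weeks.
- *The VIF check is a failed safeguard and should go.* The SAP offers it only as a collinearity check. A value such as 14.7 when language nearly coincides with site is a useful warning.
- *Every subgroup model needs DA#site.* No site link is shown for age or education.

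**Conclusion.** The point holds as a modest, inexpensive improvement to exploratory analyses. The written models omit DA#site, and for modifiers that track site a share of any site difference in the aid's effect is attributed to the modifier. The link is built in for language and indicated for delivery mode; for race/ethnicity it is possible but undocumented.

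The sizes (roughly 40-89% for Hispanic ethnicity, 71-98% for language, false-positive rates up to 17% against 2.5%) rest on assumed site mixes, and the false-positive rates also on an assumed site difference that the documents neither report nor predict. If the site difference is half the planned knowledge effect, the inflation is small, reaching at most about 5%. The primary analysis is not touched.

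**What to change.** For the race/ethnicity, language and delivery-mode models, keep the planned model and also fit it with DA#site added, for example:

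Knowledge = DA + site + race/ethnicity + DA#site + DA#race/ethnicity

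Report the DA#modifier estimate and its 97.5% interval from both. State in advance that a difference will not be attributed to the modifier itself unless it persists with DA#site in the model. Report the modifier-by-site counts so that readers can judge the link.

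Keep the VIF check as a description of collinearity only, and note the reference group used.

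This takes a few lines of SAP text and two extra terms per model, with no new data. The price is wider intervals, as shown in step 6 of the working. With DA#site included, the language interaction is identified only within San Francisco, since no other site enrols Spanish speakers. An inconclusive result there would show that language and site cannot be separated well in this sample.

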### **Inclusion Criteria**

Women are considered eligible if they are pregnant and <24 weeks gestation; planning to continue their pregnancy; 21-45 years of age; enrolled in or eligible for Medicaid; speak English or, for women recruited in San Francisco, Spanish; and are contemplating sterilization after their delivery. By focusing on women <24 weeks gestation, we hope to capture women who are still deliberating about their post-partum contraception. If the woman is eligible, the Research Assistant reviews the informed consent and receives verbal or written consent from the woman to participate in the study.

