## Sample Size Calculation

We based our sample size on the standardized mean differences (Cohen’s d) for the co-primary outcomes of knowledge (0.46) and decisional conflict (0.36) reported in the 2014 Cochrane review of decision aid RCTs. Assuming two-sided alpha levels of 0.025 (for each co-primary outcome) and 15% attrition, 175 women per arm afforded us 80% power to detect these differences.

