| Age                                                   |                                                                                                                                                                                                                                         | BL                                                           | Continuous (month/year)                                                                                                                                                                                                                                                                                                                                                                                                                                                                           | Continuous                                                                                                                                                                                                                                                                                                                                     |
| Race/ethnicity                                        |                                                                                                                                                                                                                                         | BL                                                           | 
Nominal
 
Hispanic or Latino (yes/no)
 
 
┆ Puerto Rican
 
┆ Cuban
 
┆ Mexican, Mexican American, or Chicana
 
┆ Central or South American
 
┆ Another Hispanic, Latina, or Spanish origin
 
 
Race:
 
 
┆ Black or African American
 
┆ White
 
┆ Asian
 
┆ Native Hawaiian or Pacific Islander
 
┆ American Indian or Native
 
 | 
Nominal:
 
Non-Hispanic White (ref)
 
Non-Hispanic Black
 
Hispanic/Latino
 
Other
                                                                                                                                                                                                                                  |

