### Exploratory Hypotheses

For the following exploratory hypotheses, regression will be used to test intervention effects controlling for study site. The beta coefficient and corresponding 97.5% confidence interval will be used to assess the effect of the intervention.

- **Pre- and Post-Dobbs SCOTUS Decision Exploratory Analyses:** regression analyses are adjusted for study site  
\*\*note state interaction effects below\*\*
  - Date for the *Dobbs* decision can be categorized in 3 ways:
    - Dichotomized as before June 24, 2022 and June 24, 2022 or later (the verdict)
    - Dichotomized as before May 1, 2022 and May 1, 2022 or later (the leak)
    - Categorical: before May 1; May 1- June 23; June 23 or later (would measure effect of the leaked news and then effect of the full impact)
  - How did the *Dobbs* SCOTUS decision impact recruitment?
    - Recruitment changes pre- and post-Dobbs
      - More interest in joining study
      - Differences in recruitment across gravida and parity
  - How has it affected our outcomes of interest?
    - The desire for sterilization at baseline
    - Decisional conflict about contraceptive method selection at T1 predicted by date
    - Ease in contraceptive decision making at T1 and T2 predicted by date
    - Certainty about sterilization decision at T1 and T2 predicted by date
    - Contraceptive method selected at T1 and T2 predicted by date
    - Contraceptive method used at T3 predicted by date

- **\*\*Interaction effect between date and state on all outcomes (for every outcome)\*\***

- **Additional Sensitivity Analyses for Primary and Secondary Outcomes**

- We will run additional sensitivity analyses to test robustness of the intervention effects after adjusting for any significant differences in baseline characteristics (to be identified during analysis) between the intervention and control group that are also associated with the outcomes of interest:
  - 1) sterilization knowledge at T1
  - 2) decisional conflict at T1
  - 3) contraceptive method selected at T1
  - 4) satisfaction with decision-making at T3
- We will run additional sensitivity analyses to test robustness of the intervention effects after adjusting for differences in:
  - T3 Outcomes (satisfaction with decision-making at T3):

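### Effect modification by age is tested only through an unexplained split at 25; if the aid's effect changes gradually with age, this may discard roughly 40% to 75% of the information on the interaction

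*Combined protocol and SAP*

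**What the plan says.** Under Exploratory Hypotheses, the subgroup analyses are introduced as interactions with no a priori "hypothesis, not powered) of the Primary Outcomes by" a list of baseline variables. Age appears there as "Age (categorized for this analysis: <25, 25" and over, with one model written out: "Knowledge= decision aid + site + age + DA#age". The heading covers both primary outcomes, but the age model is given for knowledge only; for race/ethnicity, both outcome models are written.

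Inclusion Criteria admit women "21-45 years of age". The table of Covariates and Baseline Characteristics lists age as "Continuous (month/year"), with a continuous structure for analysis. The split is therefore made for this analysis alone. No clinical, regulatory or statistical reason is given for 25, and no continuous interaction with age is planned.

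For the exploratory analyses the plan states: "The beta coefficient and corresponding 97.5% confidence interval will be used to assess the effect of the intervention". That corresponds to a two-sided alpha of 0.025.

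**The concern.** The cut lies near the bottom of the eligible range. The lower level covers four whole-year ages (21 to 24) of the 25 that are eligible. The upper level treats women from 25 to 45 as one group. If the aid's effect on knowledge or decisional conflict drifts with age, the interaction coefficient compares two averages and ignores the variation in age within each group.

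This is the only planned look at whether the aid works differently by age. What is at stake is the precision of that one exploratory result, and whether anything can be said about the pattern between 25 and 45. Elsewhere the plan keeps a continuous form beside a categorical one: BMI, desire for sterilization, and certainty about the sterilization decision. Age as a modifier has only the split.

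**Working it through.** **The plan's own figure.** Sample Size Calculation gives standardized differences for the "co-primary outcomes of knowledge (0.46) and decisional conflict (0.36") and continues: "Assuming two-sided alpha levels of 0.025 (for each co-primary outcome) and 15% attrition, 175 women per arm afforded us 80% power". With z(0.9875) = 2.241 and z(0.80) = 0.842, the sum is 3.083.

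- d = 0.36: 2 × (3.083/0.36)² = 146.7, so 147 per arm; 147/0.85 = 173, against the stated 175.
- d = 0.46: 2 × (3.083/0.46)² = 89.8, so 90 per arm; 106 after attrition.

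The main sample size reproduces. The plan states no figure for the age subgroup.

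**Information kept by the split.** With 1:1 allocation and an effect that is linear in age, the information on the interaction kept by the split, relative to continuous age, is the squared correlation between age and the indicator of age under 25. For uniform ages this is 3p(1 − p), with p the share under 25. With p = 4/25 = 0.16 it is 3 × 0.16 × 0.84 = 0.403, a 60% loss; 0.16 × 350 = 56 women would be under 25.

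The other rows assume normal curves truncated to 21–45. Power for the split is Φ(√kept × 3.083 − 2.241), for a trend at which continuous age would have 80% power.

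| Assumed ages (mean, SD) | Under 25 | Information kept | Loss | Power of split |
|---|---|---|---|---|
| 26.2, 3.2 | 41% | 61% | 39% | 57% |
| 27.4, 4.0 | 31% | 53% | 47% | 50% |
| 28.1, 4.1 | 26% | 49% | 51% | 47% |
| 28.8, 4.3 | 21% | 44% | 56% | 42% |
| Uniform 21–45 | 16% | 40% | 60% | 39% |
| 30.4, 4.6 | 13% | 35% | 65% | 34% |
| 32.1, 4.7 | 7% | 25% | 75% | 24% |

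These rows are scenarios, not bounds. A sample with mean 24.6 (62% under 25) would lose 33%; one with mean 33.0 and SD 4.8 (5% under 25) would lose 80%. Shape matters too: right-skewed ages with 39% under 25 keep 48%.

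**What the split can detect.** The standard error of the between-group difference in effect, in SD units, is 2/√(Np(1 − p)). With N = 350 and 80% power at alpha 0.025, the detectable difference is 3.083 × 2/√(350 × 0.16 × 0.84) = 0.90 SD at p = 0.16. It is 0.72 SD at p = 0.30 and 0.66 SD at an even split. All three exceed the assumed main effect on knowledge, 0.46.

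**What continuous age can detect.** The standard error of the slope of the effect is 2/(√N × SD of age). With N = 350 and an age SD of 4.6 (35% kept under the split):

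- 0.10 SD per 5 years: 0.02 × √350 × 4.6/2 = 0.86, so power is about 8% continuous and, with √0.35 × 0.86 = 0.51, about 4% with the split.
- 0.15 SD per 5 years: by the same steps, about 17% against 7%.
- 80% power with continuous age needs 5 × 3.083 × 2/(√350 × 4.6) = 0.36 SD per 5 years.

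A wider spread helps. With uniform ages (SD 7.21), a gradient of 0.10 SD per 5 years gives about 19% against 8%.

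**The case against.** The strongest reply is that the plan already sets expectations: the subgroup analyses are exploratory, without a prior hypothesis, and declared not powered. Nothing in the primary or secondary analyses rests on them. Fixing the cut in advance prevents a data-driven one, the text openly says the categorization is for this analysis, and education is also reduced to two levels in the same list. There is no internal contradiction. All of this stands. It limits the importance of the point, but it is not a reason to set aside data already collected.

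The best coding also depends on an unknown shape. The efficiency measure is symmetric: if the true modification is a step at 25, a linear age term keeps only the same fraction that the split keeps under a linear trend. This stands too, and it is why the split should stay.

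Four stronger readings are tempting, and the documents do not support them:

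- A reader might infer that the under-25 group is bound to be small and that over half the information is bound to be lost. Four of 25 eligible ages is not a share of participants. In the truncated-normal cases with mean about 27 or less, the loss is under half.
- A reader might infer that a gradient above 25 would be invisible. It would still move the average effect in the upper group; what is hidden is its shape.
- A reader might pick a steep gradient to make the gap look dramatic. At 0.35 SD per 5 years, simulated power is 76–79% with continuous age against 22–28% with the split. But that gradient is 0.07 SD per year. Centred on 0.46 at age 30, it implies an effect of 0.46 − 9 × 0.07 = −0.17 SD at 21 and 0.46 + 15 × 0.07 = 1.51 SD at 45. Nothing in the documents suggests this.
- A reader might infer that a null interaction will be reported as the same effect at all ages. The plan does not say so, and its own label warns against it.

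**Conclusion.** The point holds as a low-cost improvement. The plan examines effect modification by age only through an unexplained split of a variable it collects as continuous. If the effect is linear in age, the split may lose roughly 40% to 75% of the information on the interaction: 60% for uniform ages, about 39% for a mean near 26 with 41% under 25, and about 75% for a mean near 32. It also cannot show the shape of the effect between 25 and 45.

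The size rests on two assumptions that the documents do not settle: the enrolled age distribution and a linear trend. No primary or secondary conclusion is affected. With modest gradients, continuous age would still leave the interaction imprecise, so the gain is a better estimate rather than a well-powered test.

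**What to change.** In the subgroup list under Exploratory Hypotheses, specify the age interaction with age continuous (centred, in years), adjusted for site, and write the model out for both knowledge and decisional conflict. Report the interaction coefficient with its 97.5% interval, and the model-based effect of the aid at a few ages, for example 22, 25, 30, 35 and 40. Keep the prespecified under-25 against 25-and-over interaction as a secondary analysis, with a sentence giving the reason for 25 if there is one.

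The cost is a short change in wording and one additional exploratory model per outcome; no new data are needed. The linear term would be substantially less efficient than the split if the aid's effect really steps at 25, and the retained split covers that possibility.
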